##### MRS

2.4.2.3

To measure the relative concentrations of metabolites (N-acetylaspartate, creatine plus phosphocreatine, choline-containing compounds, GABA, and glutamate/glutamine) and metabolite ratios, a magnetic resonance spectroscopy J-editing sequence (45) is used with TR = 1500 ms, TE = 68 ms, and voxel size 2.5 cm^3^ for a volume of 15.6ml (close to the default of 18 ml) (45) The GABA levels are measured with an adapted version of GE’s standard PRESS sequence PROBE. The addition is a set of editing pulses that act upon resonances of 1.9 ppm and higher (45). Creatine at 3 ppm is not affected by the editing pulse but the GABA triplet at 3.1 ppm is, after a subtraction the GABA signal remains. The number of data points is 4096, sampled at 5 kHz, and the number of averages is 784 with in scanner averages NEX=2. After the scan 16 non-water-suppressed reference scans are made, resulting in a total scan time of 20 minutes.

An anatomical region of interest (ROI) is defined based on a rotated T-1 weighted anatomical scan obtained during the same scanning session, according to standard anatomical atlases. Prior to the scan, a vitamin E capsule is placed on the scalp region corresponding to the individually defined cTBS target within the left pSTC using Brainsight Neuronavigation software (Rogue Research, Canada). The voxel is placed in a rotated anatomical scan with the center in line with a vitamin E capsule during each scanning session. The voxel size was chosen to be 2.5 cm^3^ to match the approximate spread of the electric field induced by the TMS stimulation (97). To prevent lipid contamination of the skin and to cover the brain tissue underneath the skull as close as possible, the voxel is placed in a rotated anatomical scan over the anterior-posterior and inferior-superior axes, such that the face of the cubic voxel is parallel to the skull at the placement of the capsule. High bandwidth saturation pulses are used to saturate lipid signals originating from tissue close to the six faces of the cube.

##### DWI

2.4.2.4

To quantify white-matter microstructural indices of network connectivity, diffusion weighted imaging (DWI) data is acquired employing a 2D spin-echo echo-planar imaging (SE-EPI) sequence. Two scans (13 minutes each) are acquired in anterior–posterior (AP) and posterior–anterior (PA) phase-encoding directions. We use a high-angular resolution diffusion imaging (HARDI) acquisition scheme with b-values of 0 s/mm^2^ (10 gradient directions), 300 s/mm^2^ (10 gradient directions), and 1100 s/mm^2^ (60 gradient directions). Other sequence parameters include: TR = 9667 ms, TE = Minimum, slice thickness = 2 mm, 80 axial slices, a spatial resolution of 2 mm^3^.

##### fMRI

2.4.2.5

For identifying an individualized TMS target and quantifying task-based BOLD activation and task-based functional network connectivity, a 5-minute language localizer functional scan is acquired with TR = 2000 ms, TE = 30 ms, flip angle = 65 degrees, a spatial resolution of 3.0 × 3.0 × 3.0 mm^3^ and 40 slices. During the scan, participants are asked to perform an Auditory Description Decision Task (ADDT). The task consists of two block types: (1) a series of beeps interspersed within “non-sensical” sounds (English statements pronounced backward) and (2) true (correct target) and false (foil) statements (e.g., a true statement would be “Something that hangs in a museum is a painting.” And a false statement would be “Something that parts your hair is a refrigerator.”). There are a total of ten 30-second alternating blocks, beginning with block type 1. Participants are instructed to push a button when they hear a beep (block type 1 – beeps and sounds) and when the description is true (block type 2 – true/false statements). Twenty of 30 items are correct targets; 10 of 30 are foils. This task has been shown to reliably activate both superior temporal as well as inferior frontal language regions (98–100) and is recommended, based on its reliable, robust activation of language areas, for presurgical language mapping (101).

In addition to the task-related functional scan, a resting-state fMRI scan is acquired for resting-state functional connectivity analyses. During the pilot phase, the resting-state scan was acquired with a 12-minute single-shot, partially parallel, gradient-recalled echo planar sequence with sensitivity encoding, TR = 2000 ms, TE = 30 ms, flip angle = 65 degrees, a spatial resolution of 3.0 × 3.0 × 3.0 mm^3^, and 40 slices. Resting-state functional connectivity for the main phase is measured using a 12-minute hyperband, gradient-recalled multi-echo (ME = 3) sequence with TR = 2000 ms, TE = Min Full, flip angle = 65 degrees, a spatial resolution of 3.0 × 3.0 × 3.0 mm^3^, and 48 slices. A fixation cross is provided during this scan. Participants are instructed to keep their eyes open, remain as still as possible, and “think of nothing in particular”.

#### Continuous theta burst stimulation

2.4.3

As shown in **Figure 1**, each participant in the pilot phase completed two active cTBS sessions (one with MRI and one with MEG acquired immediately before and after stimulation). Participants in the main phase of the study will complete four cTBS sessions (two active and two sham). cTBS sessions are scheduled approximately once/week to avoid carry-over effects from one visit to the next. The cTBS protocol consists of bursts of three pulses of 50 Hz stimulation repeated at 200 ms intervals (5 times per second) for 40 seconds (for a total of 600 pulses). Stimulation is applied at an intensity of 80% of active motor threshold (AMT) defined as the minimum stimulator intensity required to elicit a motor evoked potential from the first dorsal interosseous muscle of at least 200 microvolt peak to peak amplitude on five out of ten trials while the participant maintains voluntary contraction of the target muscle. A neuronavigation system (Brainsight, Rogue Research, Canada) is used to track the position of the TMS coil over the stimulated target. The target is defined by combining e-field modeling (described below) with the participant’s peak BOLD activation within the left pSTC during the baseline ADDT task, overlaid on the structural anatomical scan. A functional localizer (rather than a single structurally-defined ROI) was used in this study as previous literature suggests significant interindividual variability in both typically developing individuals (102) as well as those with neurological disorders (103, 104). The feasibility of the application of TBS in the proposed study populations has also been well supported in the literature and by our own experience (65, 105–107).

In the current study, cTBS is administered using a MagPro X100 magnetic stimulator (P/N: 9016E711, Magventure A/S) and a double-sided Cool-B65 Active/Placebo (A/P) coil (P/N: 9016E0501, MagVenture A/S). Inside the A/P coil, there is a figure-of-eight winding on the active side and a metal shield on the sham side, separated by approximately 8 cm. For active stimulation, the active side of the coil is placed on the scalp; for sham stimulation, the coil is flipped, and the spacer and shield attenuate the field reaching the brain. Visually, both sides of the coil are identical, therefore blinding the TMS technician to active or sham mode. During a cTBS session, a unique patient code, supplied by MagVenture, is inputted into the MagPro X100 system, which then prompts the TMS technician to either flip or maintain coil orientation. A randomized schedule of visits was created using block randomization and the unique patient codes designating active or sham mode, and is kept in an electronic password protected document by an unblinded study staff member. The order of sessions is scheduled to ensure that the participant receives active and sham stimulation for one modality (MRI or MEG) prior to moving on to the other modality. Thus, there are only four potential orders (Active, Sham, Sham, Active; Active, Sham, Active, Sham; Sham, Active, Sham, Active; and Sham, Active, Active, Sham). The block randomization ensured that there will be the same number of participants receiving the cTBS in each of these orders.

Participants are asked to complete an Assessment of Blinding following each cTBS session to assess the integrity of the blind. During the assessment, participants are asked to guess whether they received active or sham TMS and to report their confidence in their guess on a scale from 0 (not confident at all) to 5 (extremely confident). Participants are also asked to rate the loudness and painfulness of the stimulation and to describe any facial muscle twitching or additional side effects experienced during cTBS.

#### Image processing procedures

2.4.4

##### MEG

2.4.4.1

Data is converted to MEG-BIDS (108) format using MNE-BIDS toolbox (109) and is analyzed with MNE-Python toolbox (110) for electrophysiological research, Freesurfer (111) for anatomical surface preparation, and custom scripts written in Python and Bash. The raw MEG data sets (baseline, and post stimulation for active TBS and sham TBS) for each participant undergo quality control procedures to remove trials corrupted by artifacts. Broadband evoked responses are extracted, as well as induced changes in oscillatory power in the time frequency response. Data are analyzed in both sensor space and anatomical source space. Forward modeling of the down-sampled cortical manifold is assessed using a realistic single layer boundary element model and source localization is performed using beamformer or minimum norm techniques, depending on the task. For evoked responses, source localized time series amplitude and latency (defined as the time interval between stimulus and maximal amplitude) are determined. For induced power analyses, the peak induced gamma frequency will also be determined. In the context of the M100/M50 task, two components are identified – the M50 and the M100, both occurring in Heschl’s gyrus, in left and right superior temporal cortices. In the speech processing oddball paradigm, the mismatch negativity is identified as the difference between the evoked responses to the frequent and rare tones. For the auditory steady state experiment, inter-trial coherence is calculated as described in (112).

##### MRS

2.4.4.2

Custom software is used to measure the relative concentrations of metabolites (N-acetylaspartate, creatine plus phosphocreatine, choline-containing compounds, GABA, and glutamate/glutamine) and metabolite ratios. The data is pre-processed with an eddy current correction and the data is tested for patient movement by tracking the residual water signal, edit - non edit pairs with residual water deviations larger than 10% are rejected (45). Subsequently, the averages of the data are frequency and phase corrected before summation (113). In a last step, the summed data is fitted with simulated reference signals for the non-edited, the edited, and the subtracted data (113). Standard statistical packages such as Statistica are used to determine significant differences in the metabolites taken immediately prior to and immediately following cTBS administration. In-house software was written to derive ratios of GABA and glutamate to creatine.

##### DWI

2.4.4.3

DWI data undergo processing using multiple software tools, including MRtrix3 (114), FSL (115), Freesurfer (116), ANTS (117), and TractSeg (118). The anterior–posterior (AP) and posterior–anterior (PA) phase-encoding scans are concatenated. Marchenko-Pastur principal component analysis (PCA) are used to denoise the DWI data via the MRtrix3 *dwidenoise* function, followed by removing Gibbs ringing artifacts using the MRtrix3 *mrdegibbs* function. Eddy current correction are performed using the MRtrix3 *dwifslpreproc* function, utilizing the FSL linear second-level model (*–slm=linear*) and the default outlier replacement (*–repol*) parameters. Additionally, bias field correction is applied using both MRtrix3 and ANTs software *dwibiascorrect ants*. To increase anatomical contrast and improve tractography results, the DWI images are up-sampled to an isotropic voxel size of 1.25 mm using *mrgrid*. Whole-brain masks are generated from the up-sampled images using FSL Brain Extraction Tool 2, *bet2*, with a 0.3 fractional intensity threshold. The basis function for multi-tissue types (white matter (WM), gray matter (GM), and cerebrospinal fluid (CSF)) are derived using Dhollander’s algorithm, *dwi2response dhollander*, to estimate the fiber orientation densities (FODs) within each voxel. To perform multi-shell and multi-tissue analysis, the basic functions for each tissue type are applied to the DWI data using the MRtrix3 *dwi2fod msmt_csd* function. For group-level analysis, the FODs are normalized. The peaks of the WM FODs are extracted from each voxel using *sh2peaks*.

To investigate specific white matter tracts, the left and right arcuate fasciculus and auditory radiation fiber bundles are extracted using the WM peaks with an automatic fiber tracking package, TractSeg, in conjunction with FSL XTRACT atlas (119). TractSeg uses deep machine learning algorithms to extract these fiber bundles. Finally, a tensor model is fitted using *dwi2tensor* and the fractional anisotropy (FA), axial diffusivity (AD), radial diffusivity (RD), and mean diffusivity (MD) maps are created using *tensor2metric* and average values are extracted for specific tracts.

##### Task-based fMRI

2.4.4.4

Afni (version 22.3.05) (120) is used to process the task-based fMRI data, afni_proc.py is used to setup a full pipeline for the fMRI analysis of each participant, including the automatic generation of a quality control HTML for evaluating the data and processing steps (121). The first 14 TRs (28 seconds) are discarded from the analysis to allow stabilization of the magnetic field and noise cancellation. All images are corrected for slice acquisition timing, motion corrected to the minimum outlier volume, and spatially smoothed with a 4mm full-width-half-maximum smoothing kernel. EPI-anatomical alignment is performed using the lpc+ZZ cost function (122) with local EPI unifizing for additional stability, and these datasets are checked for left-right consistency (123). To reduce effects of participant motion, volumes with large motion (Enorm > 0.3 mm between successive time points) are censored. A block regression basis is used, in which the onset of the true/false statement blocks are defined. The contrast between those blocks (block type 2) and implicit baseline (block type 1 – beeps and sounds) are computed. Several steps are then performed for quality control evaluation such as checking the alignment between the anatomical, EPI, and template image; checking that the stimuli are properly assigned between each stimulus class; and checking how many data points are censored because of motion. The final language (block type 2) > implicit baseline (block type 1) statistical map and the participant anatomical scan are then loaded into the Brainsight Neuronavigation system (Rogue Research, Canada). The 3dClusterize command is then used on the t-statistical map to extract the coordinates of the peak activation in the Wernicke area for each participant and is chosen as the cTBS target. For the ASD main phase of the study, a mask will be used to constrain the choice of the stimulation target. The mask was generated by selecting seven ROIs from the Sensaas atlas (https://github.com/loiclabache/SENSAAS_brainAtlasL: SMG7, T1_4, STS2, STS3, STS4, T2_3, T2_4), and merging them into a single ROI (see **Figure 2B**). E-field modeling is an additional step for the main phase and will be added to further refine the cTBS target and optimize delivered dosage. The induced e-field with the figure of eight coil used in the current study is estimated to be approximately 2.5 cm^3^ (97).

**Figure 2 f2:**
[figure not shown]
**(A)** Individualized cTBS targets during the pilot phase of the study were based on peak BOLD activation during the ADDT, a language task. The choice of cTBS target will be constrained during the ASD main phase of the study. This will be done using **(B)** a mask generated from merging seven individual ROIs from the Sensaas atlas (e.g., SMG7, T1_4, STS2, STS3, STS4, T2_3, T2_4).

To perform e-field modeling, first, the mri2 mesh pipeline within the Simulation of Noninvasive Brain Stimulation (SimNIBS) version 3.2.1 software (124) is used to construct computational head models to determine the induced E-field at the individualized target based on the peak BOLD activation from the task. Then, the targeting and analysis pipeline (TAP) software (125) add-on is used to determine the optimal TMS coil placement on the scalp. A voxel containing the individualized target in an otherwise empty MRI image file is inputted into the TAP software. The TAP software uses the computational head model generated by the SimNIBS and determines the closest point in the sulci wall and its normal vector. This normal vector, which is perpendicular to sulci wall, is used in SimNIBS to find the TMS coil placement which maximizes the E-field going into the sulci wall known to cause the best stimulation effect (126). The search for this optimal TMS coil placement is performed on the scalp surface grid (accounting for 2mm hair thickness) with 1 mm edge length (1-degree TMS orientation increments) in a circular area (with radius of 25 mm) around the scalp-projected point of the coordinate. This optimal coil setup is saved to a text file and is then used with the Brainsight Neuronavigation system (Rogue Research, Canada) during the session.

We also perform a psychophysiological interaction analysis with the CONN toolbox to study the functional connectivity changes, using the same seed regions. For each pair of seed and target areas, a generalized psychophysiological interaction model (gPPI (127, 128)) is defined with seed BOLD signals as physiological factors, boxcar signals characterizing each individual task condition convolved with an SPM canonical hemodynamic response function as psychological factors, and the product of the two as psychophysiological interaction terms. Functional connectivity changes across conditions are characterized by the Fisher-transformed semi partial correlation coefficient of the psychophysiological interaction terms in each model. Finally, group-level analyses are performed using a General Linear Model (GLM (129)). For each individual voxel a separate GLM is estimated, with first-level connectivity measures at this voxel as dependent variables (one independent sample per subject and one measurement per experimental condition), and groups or other subject-level identifiers as independent variables. Voxel-level hypotheses are evaluated using multivariate parametric statistics with random-effects across subjects and sample covariance estimation across multiple measurements. Inferences are performed at the level of individual clusters (groups of contiguous voxels). Cluster-level inferences are based on parametric statistics from Gaussian Random Field theory (130, 131). Results are thresholded using a combination of a cluster-forming p < 0.001 voxel-level threshold, and a familywise corrected p-FDR < 0.05 cluster-size threshold (132).

##### Resting-state fMRI

2.4.4.5

Analysis of functional connectivity between predefined ROIs within the dorsal and ventral language networks (i.e. pSTC, posterior inferior temporal cortex, temporal-parietal junction, and inferior frontal gyrus) is performed using CONN toolbox (133) (RRID : SCR_009550) release 22.a (134) and SPM (135) (RRID : SCR_007037) release 12.7771.

Functional and anatomical data are preprocessed using a flexible preprocessing pipeline (136), including realignment, outlier detection, direct segmentation, MNI-space normalization, smoothing, and denoising. For resting state connectivity, seed-based connectivity maps (SBC) and ROI-to-ROI connectivity matrices (RRC) are estimated with 164 HPC-ICA networks (134) and Harvard-Oxford atlas ROIs (137). Functional connectivity strength is represented by Fisher-transformed bivariate correlation coefficients from a weighted general linear model (weighted-GLM (138)), defined separately for each pair of seed and target areas, modeling the association between their BOLD signal time series.

### Statistical analysis

2.5

Multiple linear regressions will be conducted to evaluate whether baseline MRS measures of local GABA and glutamate concentration, structural topography/connectivity, and/or functional activity/connectivity explain a significant proportion of the variability in MEG measures of auditory/language processing. These analyses will quantify the relationship between these measures and to what extent they may contribute to a fusion biomarker model for language processing deficits in ASD (e.g., (139)). To evaluate the effect of a single session of cTBS on MRS, fMRI, and MEG outcome measures, Factorial ANCOVAs will be conducted with time-point (pre-post) and condition (active, sham) as within-subjects variables. Other anticipated covariates in these analyses include age, gender, baseline symptom severity, and medication use. In addition to the targeted region (left pSTC), we will repeat the planned fMRI BOLD and connectivity analyses using right pSTC, left and right IFG, and a non-connected (control) cortical visual network with a temporal and frontal node to explore the spread of the effect of the cTBS from the targeted region to other structurally and functionally connected regions compared to a control network. Pearson correlation coefficients will be used for the exploratory analyses, to characterize the relationship between the neuroimaging and electrophysiological indices and baseline behavioral symptom presentation including assessments of general functioning, autism symptom severity, and auditory and language processing. As there may be intrasubject variability in these measures (independent of the cTBS intervention), we will evaluate the reliability of the baseline/pre-stimulation MEG, MRS, and fMRI outcomes by calculating the interclass correlation coefficient (Model: 2-way mixed effects, Type: mean of k measurements and Definition: absolute agreement) as a measure of test-retest reliability.

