## Abstract

It has been suggested that aberrant excitation/inhibition (E/I) balance and dysfunctional structure and function of relevant brain networks may underlie the symptoms of autism spectrum disorder (ASD). However, the nomological network linking these constructs to quantifiable measures and mechanistically relating these constructs to behavioral symptoms of ASD is lacking. Herein we describe a within-subject, controlled, proof-of-mechanism study investigating the pathophysiology of auditory/language processing in adolescents with ASD. We utilize neurophysiological and neuroimaging techniques including magnetic resonance spectroscopy (MRS), diffusion-weighted imaging (DWI), functional magnetic resonance imaging (fMRI), and magnetoencephalography (MEG) metrics of language network structure and function. Additionally, we apply a single, individually targeted session of continuous theta burst stimulation (cTBS) as an experimental probe of the impact of perturbation of the system on these neurophysiological and neuroimaging outcomes. MRS, fMRI, and MEG measures are evaluated at baseline and immediately prior to and following cTBS over the posterior superior temporal cortex (pSTC), a region involved in auditory and language processing deficits in ASD. Also, behavioral measures of ASD and language processing and DWI measures of auditory/language network structures are obtained at baseline to characterize the relationship between the neuroimaging and neurophysiological measures and baseline symptom presentation. We hypothesize that local gamma-aminobutyric acid (GABA) and glutamate concentrations (measured with MRS), and structural and functional activity and network connectivity (measured with DWI and fMRI), will significantly predict MEG indices of auditory/language processing and behavioral deficits in ASD. Furthermore, a single session of cTBS over left pSTC is hypothesized to lead to significant, acute changes in local glutamate and GABA concentration, functional activity and network connectivity, and MEG indices of auditory/language processing. We have completed the pilot phase of the study (n=20 Healthy Volunteer adults) and have begun enrollment for the main phase with adolescents with ASD (n=86; age 14-17). If successful, this study will establish a nomological network linking local E/I balance measures to functional and structural connectivity within relevant brain networks, ultimately connecting them to ASD symptoms. Furthermore, this study will inform future therapeutic trials using cTBS to treat the symptoms of ASD.

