	AD	1.24 ± 0.03 (n=19)

GABA and Glutamate concentrations are measured over creatine. The MRS voxel was centered on the individualized cTBS target as defined by the peak bold activation to the ADDT task. Voxels were 2.5 cm cubed, thus the value represents relative concentrations of metabolites within the posterior superior temporal cortex.

Mean and standard deviation values for Evoked Gamma Power and FA are dimensionless.

Mean and standard deviation values for MD, RD, and AD are measured in 10^-3^ mm^2^/s.

Sample sizes varied based on data quality and visit completion.

FA, Fractional Anisotropy; MD, Mean Diffusivity; RD, Radial Diffusivity; AD, Axial Diffusivity.

For the main phase, ASD individuals must meet the following inclusion criteria: (1) Age 14-17, (2) Community diagnosis of ASD based on DSM-IV or DSM-5 criteria, (3) FSIQ > 70, (4) Right-handed, and (5) Normal hearing. In addition to the exclusion criteria listed above for the pilot phase of the study, in the main phase individuals with known genetic disorders associated with the ASD diagnosis or that in the opinion of the investigator may increase the risk to the participant or compromise the integrity of the data will also be excluded. In the main phase of the study, we will acquire the same baseline assessments as in the pilot phase as well as additional behavioral/neuropsychological assessments related to their ASD diagnosis and their receptive and expressive language skills. Participants will also complete an audiometric evaluation to confirm that they have normal hearing. To reduce burden to the participant these baseline visits can be further divided. Additionally, each ASD participant will receive both active and sham cTBS on two separate sessions, combined with MRI and combined with MEG for a total of four imaging/cTBS visits instead of the two in the pilot phase.

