### Power analyses and sample size determination

2.3

The first aim of the study is to establish the relationship between local GABA and glutamate neurotransmitter concentrations, structural and functional network connectivity, and physiological measures of auditory/language network functioning. The estimated effect size for this aim is approximately 0.2223. This is estimated based on the literature showing a significant correlation between GABA+/Cre concentration and MEG evoked gamma power that range from 0.37-0.53 (49, 52, 56, 80). To our knowledge there is not any existing data on the correlation between the other predictor variables (DWI or functional MR connectivity) and MEG power and latency of evoked fields. However, given that both of these neuroimaging predictor variables have been shown to be aberrant in adolescents with ASD and reflect network-level structural and functional dysfunction, we predict a correlation between these neuroimaging measures and the proposed MEG measure of at least 0.15. Thus, in order to maintain 80% power with a type-I error rate of 5% and a type-II error rate of 20% we will enroll 86 ASD participants with a planned evaluable N=55 accounting for attrition.

The second aim of the study is to evaluate target engagement and the acute effects of active cTBS compared to sham cTBS on auditory/language network functioning. With planned evaluable N=55 and the minimal detectable effect (given Lehr’s equation (81)), the minimum detectible effect size is 0.38 standard deviation units, between a small (.2) and medium (.5) effect size in Cohen’s effect size taxonomy (82). We believe this is a reasonable effect size to expect given the literature. A recent study found an effect size of 0.7 on MRS GABA+/Cre concentration and 0.39 on MEG indices of sensory (visual) processing immediately following a single session of cTBS [95]. Therefore, we believe this aim is adequately powered.

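### Aim 1 is worded to use baseline measures only, although repeated unstimulated MRS, fMRI and MEG values are collected; averaging them is a cheap gain in power, not the repair of an error

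*Protocol article*

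**What the plan says.** Section 2.5 describes the Aim 1 analysis: "Multiple linear regressions will be conducted to evaluate whether baseline MRS measures of local GABA and glutamate concentration", together with structural and functional measures, account for variability in the MEG measures.

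The Abstract says that "MRS, fMRI, and MEG measures are evaluated at baseline and immediately prior to and following cTBS". Section 2.2 adds that "each ASD participant will receive both active and sham cTBS on two separate sessions, combined with MRI and combined with MEG". Each modality therefore has up to three unstimulated measurements per participant: baseline, pre-active and pre-sham. DWI is described as a baseline measure only.

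The pooled set appears once more in section 2.5, where "we will evaluate the reliability of the baseline/pre-stimulation MEG, MRS, and fMRI outcomes" by an intraclass correlation (ICC) defined for the mean of several measurements. The same sentence recognises that these measures may vary within a subject for reasons unrelated to cTBS.

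Section 2.3 sizes Aim 1 without mentioning repeated measurement or reliability: "The estimated effect size for this aim is approximately 0.2223".

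**The concern.** Section 2.5 uses one term for the regression inputs (baseline) and a wider one for the reliability analysis (baseline and pre-stimulation). The natural reading is that Aim 1 uses the baseline visit and sets the other unstimulated scans aside.

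If so, visit-to-visit noise enters both sides of the regression. Section 2.2 describes MRS and MEG baseline visits as separate, so their errors are probably close to independent, and independent errors pull the observed correlation towards zero. The average-of-k ICC would then describe a more reliable quantity than the one analysed. A participant whose baseline scan fails might also be lost even though another unstimulated scan is usable. In the pilot, Table 2 shows left pSTC MRS for 10 of 20 participants and left M100 latency for 10 of 20, with differing numbers attributed to data quality and visit completion.

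At stake are precision and some evaluable participants in an aim that has little margin over its 80% target.

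**Working it through.** **1. Reproduce the plan's own figure.** Inputs from section 2.3: "significant correlation between GABA+/Cre concentration and MEG evoked gamma power that range from 0.37-0.53"; "we predict a correlation between these neuroimaging measures and the proposed MEG measure of at least 0.15"; and "a type-I error rate of 5% and a type-II error rate of 20% we will enroll 86 ASD participants with a planned evaluable N=55". Take 0.37 for MRS and 0.15 each for DWI and functional connectivity, with uncorrelated predictors:

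R² = 0.37² + 0.15² + 0.15² = 0.1369 + 0.0225 + 0.0225 = 0.1819

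f² = R²/(1 − R²) = 0.1819/0.8181 = 0.2223, which matches.

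For the overall F test with three predictors (noncentrality f² × N, degrees of freedom 3 and N − 4), the minimum N for 80% power is 54, and power at N=55 is 81.6%. With four predictors at the same f², for example if GABA and glutamate enter separately, the minimum N is 59 and power at N=55 is 76.8%.

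**2. Effect of averaging k measurements.** If single-scan reliability is ρ, Spearman-Brown gives

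ρₖ = kρ / (1 + (k − 1)ρ).

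The expected observed correlation is multiplied by √(ρₖ/ρ) for each averaged variable. That is ρₖ/ρ when both sides are averaged (MRS or fMRI with MEG), and √(ρₖ/ρ) when only MEG is averaged (DWI with MEG).

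Example with ρ = 0.7 and k = 3: ρ₃ = 2.1/2.4 = 0.875. The two-sided factor is 0.875/0.7 = 1.250 and the one-sided factor is √1.250 = 1.118. The correlations become 0.463 (MRS), 0.188 (fMRI) and 0.168 (DWI), and f² = 0.383.

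**3. Results at N=55, three predictors.** The article gives no single-scan reliability, so 0.5 to 0.9 is assumed, equal for MRS, fMRI and MEG. The values 0.37 and 0.15 are taken as single-scan correlations.

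| Assumed reliability | ρ₃ | 0.37 becomes (k=3) | f² (k=3) | Power, k=3 | Power, k=2 |
|---|---|---|---|---|---|
| 0.5 | 0.750 | 0.555 | 0.646 | 99.9% | 98.9% |
| 0.6 | 0.818 | 0.505 | 0.486 | 99.3% | 97.2% |
| 0.7 | 0.875 | 0.463 | 0.383 | 97.2% | 94.4% |
| 0.8 | 0.923 | 0.427 | 0.313 | 93.3% | 90.7% |
| 0.9 | 0.964 | 0.396 | 0.261 | 87.9% | 86.4% |

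The smallest bivariate correlation detectable with 80% power, on the single-scan scale, falls from 0.370 to 0.247 (reliability 0.5), 0.296 (0.7) or 0.345 (0.9) with k = 3.

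**4. If fMRI is not repeated.** The fMRI term then gains only the one-sided factor, as DWI does. At reliability 0.5, R² = 0.555² + 2 × 0.184² ≈ 0.376 and f² ≈ 0.60, against 0.646. At 0.9, R² = 0.396² + 2 × 0.155² ≈ 0.205 and f² ≈ 0.26, little changed. Most of the gain comes from the MRS-MEG pair.

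**5. Exposure to earlier active stimulation.** Section 2.4.3 gives four orders (A active, S sham), used equally, with one modality completed before the other. Sessions that follow at least one active session: ASSA 3, ASAS 3, SASA 2, SAAS 2. The total is 10 of 16. In every order sessions 3 and 4, both pre-stimulation scans of the second modality, are among them.

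**The case against.** The strongest reply is that nothing here is wrong. The plan reaches its power target without averaging and uses the low end of the cited correlations. Relating the measures before the system is perturbed is the stated design. That stands: this is a gain in efficiency, and a reader who inferred that Aim 1 is underpowered by its own assumptions would be mistaken.

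A reader might also infer that the plan commits Aim 1 to a single baseline scan per modality. The text does not say so. It says only baseline measures, and the image-processing section for MEG (2.4.4.1) lists data sets as baseline and post-stimulation, which leaves open whether baseline there includes the pre-stimulation recordings. An average-of-k ICC is also compatible with an intention to average. The construction of the variable may be settled in an analysis plan that is not at hand. Baseline-only remains the natural reading, and no passage says that a mean enters the regression.

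Carry-over is a fair objection, because the averaged variable would draw largely on sessions after active cTBS, unequally for MRI and MEG according to order. Against that, the Introduction puts single-session effects at under two hours, section 2.4.3 spaces sessions about a week apart to avoid carry-over, and the active-sham comparison in Aim 2 already depends on that washout. A sensitivity analysis can check it.

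Finally, the gain is neither uniform nor free of conditions. DWI is not repeated, and the Abstract does not say whether task fMRI, resting fMRI or both are. With 86 enrolled and 55 evaluable, a planned loss of 36%, some participants may have fewer than three values, so k would range from 1 to 3 and measurement error would differ between participants.

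**Conclusion.** The point holds as a worthwhile, inexpensive improvement. As worded, Aim 1 draws on baseline measures, while up to two further unstimulated measurements of MRS, fMRI and MEG per participant are named only for a reliability coefficient. Averaging raises the expected observed correlation and lowers the minimum detectable one. At N=55 with three predictors, power moves from 81.6% to between 87.9% and 99.9% with three measurements, or between 86.4% and 98.9% with two.

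The direction is secure; the size is not. It rests on an assumed reliability of 0.9 to 0.5, equal across modalities, errors independent between visits, no carry-over, and the same k for everyone. The three-measurement figures are therefore a best case, and at high reliability the gain is modest. It is smallest for DWI, where only the MEG side can be averaged. How many participants would be recovered after a failed baseline scan cannot be estimated from the article.

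**What to change.** Before analysis, state which values enter Aim 1. The suggested primary variable is each participant's mean of all usable unstimulated values (baseline, pre-active, pre-sham) for MRS, MEG and whichever fMRI measures are repeated, with DWI kept as its single baseline value. A mixed or latent-variable model is an alternative that handles unequal numbers of measurements directly.

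Keep the baseline-only regression as a sensitivity analysis and, optionally, add one restricted to scans taken before any active session. Report the single-measurement ICC beside the average-of-k ICC, so that the reliability quoted matches the values analysed. Clarify which fMRI scans are repeated before stimulation, and whether baseline in the MEG processing section includes the pre-stimulation recordings.

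The cost is wording in the analysis plan and a little more modelling: no new scans, visits or participants. The price in assumptions is that Aim 1 would share Aim 2's reliance on washout, and that k will vary with attrition.
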